### Photobiomodulation

2.9

PBM will be applied with extra and intraoral LED devices. The LED plates speed up the treatment as they deliver all the energy at once, having the advantage of radiating several points at the same time. The applications of both will occur in the following experimental periods after the completion of the surgeries: immediate postoperative, 1, 2, 7, 14, 30, 60, and 90 days.

#### Extraoral PBM

2.9.1

Extraoral PBM will be applied with a mask (Cosmedical, São Paulo, Brazil) containing 57 red LEDs and 74 infrared LEDs, in the parameters described in Table 2 and in the periods described previously.

**Table 2 T2:**
[figure not shown]
Extraoral LED mask dosimetric parameters.

#### Intraoral PBM

2.9.2

Participants will receive intraoral LED with a specially designed oral device (Cosmedical) with the parameters described in Table 3, in the periods described above (the same as for extraoral irradiation).

**Table 3 T3:**
[figure not shown]
Dosimetric parameters of the intraoral LED device.

## Outcome measures

3

All variables will be evaluated by the same 2 examiners, before and after surgery for periods of 1 to 120 days according to each variable. The primary outcomes of the study are: the occurrence and intensity of pain and edema (with evaluation periods of 1, 2, 7, and 14 days after surgery), the occurrence of paresthesia (with evaluation periods of 7, 30, 60, 90, and 120 days after surgery) and bone repair in the anterior palatine suture region (with evaluation periods of 30, 60, 90, and 120 days after surgery). The secondary outcomes of the study are: headache, otalgia, nausea, hematoma, nasolacrimation, nasal bleeding, and surface temperature (with evaluation periods of 1, 2, 7, and 14 days after surgery), dysphagia (with evaluation periods of 7 and 30 days after surgery), anxiety (7 days after surgery), quality of life (with periods of evaluations of 7 and 30 days after surgery), and use of analgesics and anti-inflammatory drugs on the 14th day. Information on gender (male/female), race, age (in years), and educational background (from illiterate to full graduate) will also be collected.^[22,23]^

### Pain evaluation

3.1

Visual analog scales (VASs) are the most commonly used instruments for postoperative pain measurement after oral surgery using PBM postoperatively.^[22,24,25]^

On the other hand, the Numeric Pain Rating Scale (NRS)-101 scale is also being used to measure pain resulting from these surgeries^[26,27]^ and maybe more advantageous than that of VAS.

Both scales will be applied. VAS will be printed and the research participants will be instructed by the evaluators to mark a point in the 10 cm line, indicating the intensity of their pain after 1, 2, 7, and 14 days of surgeries. For NRS-101, the 2 examiners will ask participants to assign a number between 0 (no pain) and 100 (worst possible pain) that best represents the pain they are experiencing, in the same experimental periods.

### Edema evaluation

3.2

To measure this outcome, the previous facial measures described in item 2.6.1., considered time 0 (T0), will be remade in the postoperative periods of 1, 2, 7, and 14 days, by the same 2 examiners who did the initial measurements. The edema of each participant will be defined as the difference between the sum of the measures of the 5 lines (of both sides) in each experimental period, and the sum of the same 5 lines before the surgery (T0).

### Global sensitivity index

3.3

The sensitivity tests described above will be repeated in all participants, on both sides on postoperative days 7, 30, 60, 90, and 120. The results of the light touch and sting sensation tests will be added (maximum value 5 points/side/participant/period) and this value will be called qualitative sensitivity. On the other hand, the measurements obtained in the static 2-point discrimination test (item 2.6.5) and dynamic 2-point discrimination test (item 2.6.6) in each experimental period will be subtracted from those obtained in the respective tests in the preoperative evaluation and the value of the difference between these measures will be classified according to Table 4. The value of the sum of the classifications obtained in the static 2-point discrimination test (item 2.6.5) and dynamic 2-point discrimination test (item 2.6.6) in each experimental period will be denominated quantitative sensitivity (summing 0–10 points/side/participant/period).^[13,16]^

**Table 4 T4:**
[figure not shown]
Classification for the differences obtained in the static 2-point discrimination test and dynamic 2-point discrimination test in the different periods.

Finally, the global sensitivity index (GSI) for each side of each participant in each experimental period will be calculated by adding the value of the qualitative sensitivity (sum of the light touch and stinging sensation) to the value of the quantitative sensitivity (sum of the classification obtained in the static 2-point discrimination test (item 2.6.5) and dynamic 2-point discrimination test (item 2.6.6)), its maximum value is equal to 15. The GSI will be classified according to Table 5, will be computed by hemi face in each experimental period, and may vary from normal sensitivity to reduced sensitivity.

**Table 5 T5:**
[figure not shown]
Classification for the differences obtained in GSI in the different periods.

### Bone repair evaluation

3.4

Periapical radiographs will be obtained from each participant, as described previously, after 30, 60, 90, and 120 days of surgeries. The OD of the alveolar bone in the anterior region of the palatine suture, in each experimental period, will be calculated and compared with that obtained in the preoperative radiographic examination. Images will be scanned and analyzed with Image J software (NIH).

### Secondary outcomes evaluation

3.5

The variables: local and systemic temperature, occurrence of headache, otalgia, nausea, hematoma, nasolacrimation, nasal bleeding, and the use of analgesics and anti-inflammatories will be evaluated in the periods of 1, 2, 7, and 14 days after surgery.

The temperature will be measured locally (on both sides) and systemically. The local measurements will be made with an infrared digital thermometer (model TL-612, Techline Comercial Importadora Exportadora e Serviços Ltda, São Paulo, Brazil) in the region of right and left cheeks and anterior nasal spine. The systemic temperature will be measured in the frontal region of the patient, in the median position, 3 cm above the glabella.

The presence of hematoma/ecchymosis will be evaluated by measuring the largest diameter of the colorimetric changes on the right and left side. The measure will be performed by the examiners, who will classify the occurrence of this result into 4 categories:

(1)none;(2)larger diameter smaller than 4 cm;(3)larger diameter between 4 and 10 cm, and(4)larger diameter larger than 10 cm.^[28]^

For the analysis of anxiety, the same questionnaire described for the initial evaluation will be applied 7 days postoperatively. Saliva analysis will also be performed at these same times.

The variables: dysphagia and impact of the procedure on the quality of life of the participant will be evaluated in the periods of 7 and 30 days after surgery.

The evaluation of dysphagia will be performed after 7 and 30 days by questioning and classification on a numerical scale in which:

(0)total absence of dysphagia;(1)dysphagia to solid foods;(2)dysphagia to any liquid or solid food.

The impact of the surgical procedure on the participants’ quality of life will also be evaluated. The examiners will ask the participants to answer yes or no to the following 10 questions, after 7 and 30 days of the surgeries.^[29,30]^

(1)Are you maintaining your social activities normally?(2)Are you working/studying normally?(3)Are you maintaining your normal diet?(4)Do you have difficulty swallowing because of the surgery?(5)Do you have difficulty in tasting food?(6)Can you chew on the sides?(7)Do you have trouble sleeping because of the surgery?(8)Did you have trouble speaking because of the surgery?(9)Has your appearance changed because of the surgery?(10)Do you feel sick from the surgery?

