### Sample calculation

2.4

To determine the number of participants in each experimental group, a sample calculation based on the variability of the results of 3 articles that evaluated the main outcomes of this study in similar situations was performed.^[12–14]^ Using the unpaired *t* test method ^[15]^ the required sample would be 66 individuals, 33 per group. Calculations were performed using a significance level of 0.05 (implying a 5% Type I error and resulting in a 95% confidence interval analysis) and an absolute error of 5%. Considering a 10% loss, a loss of 3 participants per group should be predicted, thus, 72 patients will be recruited, 36 per group.

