### Statistical analysis

3.6

Initial descriptive analyses will be performed considering all variables measured in the study, both quantitative (mean and standard deviation) and qualitative (frequencies and percentages). Later, the appropriate statistical tests will be applied for each specific analysis. In all tests, the significance level of 5% probability or the corresponding *P*-value will be adopted. All analyses will be performed using the statistical software SAS for Windows, version 9.1.

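### Hematoma diameter is measured on each side but the outcome is defined as four wide classes; comparing the arms on the centimetre value would usually be more informative and costs almost nothing

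*Protocol article*

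**What the plan says.** Section 3.5 (Secondary outcomes evaluation) describes two steps. First, a length is measured: "The presence of hematoma/ecchymosis will be evaluated by measuring the largest diameter of the colorimetric changes on the right and left side". Then that length is graded: "The measure will be performed by the examiners, who will classify the occurrence of this result into 4 categories". The grades are none, under 4 cm, and then "larger diameter between 4 and 10 cm, and(4)larger diameter larger than 10 cm". A published source is cited for the scale.

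Section 3 (Outcome measures) places hematoma among the secondary outcomes: "The secondary outcomes of the study are: headache, otalgia, nausea, hematoma, nasolacrimation, nasal bleeding, and surface temperature", assessed at days 1, 2, 7 and 14.

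Section 3.6 (Statistical analysis) plans means and standard deviations for quantitative variables and frequencies for qualitative ones. It names no test for this variable: "Later, the appropriate statistical tests will be applied for each specific analysis".

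The article gives no expected diameter, standard deviation, class frequency or treatment difference for hematoma.

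**The concern.** A length in centimetres is obtained on each side, but the only outcome defined from it is a class. The third class is 6 cm wide, so a treatment that shrinks bruises from about 9 cm to about 5 cm would leave every such participant in the same class. Any effect that does not carry participants across 4 cm or 10 cm, or to none, is invisible on this scale.

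Facial edema is also measured in length units, by the same two examiners on the same four days, and section 3.2 keeps it as a continuous change from baseline. The grading of hematoma is therefore a stated choice for this variable and not a general feature of the plan.

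At stake is the precision of one secondary comparison. If most participants share a class at a visit, that comparison says little about bruise size. A diameter that is not written down at the visit cannot be recovered later.

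**Working it through.** **Plan's own figure.** The only size figure is in section 2.4: "the required sample would be 66 individuals, 33 per group", with "Calculations were performed using a significance level of 0.05". It was derived from the main outcomes, not from hematoma. It cannot be rebuilt, because the effect, standard deviation and power are not given. At an assumed 80% power it would correspond to a standardised difference of (1.96 + 0.84) × √(2/33) ≈ 0.69. Below it serves only as the number analysed per group.

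**Inputs.** From the documents: 33 per group, alpha 0.05 (taken as two-sided), and class limits none / under 4 / 4–10 / over 10 cm. Assumed, because the documents give nothing: a share with no bruise, log-normal diameters otherwise, and one value per participant.

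**Method.** Simulate 3000 trials per scenario and apply the Mann-Whitney test to the diameter (0 if none) and to the four classes. For efficiency, compute in a very large sample the difference in mean rank between arms divided by the standard deviation of the ranks. Efficiency kept = (that ratio for classes ÷ that ratio for diameter)².

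**Set 1: different kinds of effect.** Medians are among those with a bruise, control vs treated.

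| Assumed situation | Power, diameter | Power, classes | Efficiency kept |
|---|---|---|---|
| Spread, 5 vs 3.33 cm, log-SD 0.6, 10% none | 0.56 | 0.44 | 73% |
| Spread, 6 vs 3.6 cm, log-SD 0.8, 15% none | 0.42 | 0.35 | 78% |
| Large, 9 vs 6.5 cm, log-SD 0.45, 2% none | 0.76 | 0.63 | 74% |
| Size and presence, 4.5 vs 3 cm, log-SD 0.6, 10% vs 25% none | 0.81 | 0.73 | 82% |
| Nearly all under 4 cm, 2 vs 1.4 cm, log-SD 0.5, 10% none | 0.60 | 0.08 | 8% |
| Nearly all 4–10 cm, 6.5 vs 5.5 cm, log-SD 0.22, 2% none | 0.80 | 0.19 | 18% |
| Presence only, 3 cm, log-SD 0.5, 10% vs 40% none | 0.57 | 0.66 | 119% |
| Presence only, 2 cm, log-SD 0.5, 60% vs 85% none | 0.61 | 0.62 | 103% |

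The first four rows lose 18 to 27%. The next two, with 83 to 94% of each arm in one class, lose 82 to 92%. The last two lose nothing; there the classes do slightly to moderately better than the diameter.

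**Set 2: a pure size shift of 0.75 log-SD, same share with none in both arms.** Efficiency is recovered from power as ((1.96 + z of power on classes) ÷ (1.96 + z of power on diameter))². For the first row: z(0.74) = 0.643 and z(0.57) = 0.176, so (2.136 ÷ 2.603)² = 0.67.

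| Control median, log-SD, share none | Diameter | Classes | Kept | Largest class, arms pooled |
|---|---|---|---|---|
| 5 cm, 0.4, 5% | 0.74 | 0.57 | 67% | 52% |
| 6 cm, 0.3, 5% | 0.74 | 0.41 | 44% | 75% |
| 6 cm, 0.4, 10% | 0.64 | 0.45 | 63% | 60% |
| 5 cm, 0.6, 10% | 0.64 | 0.51 | 73% | 45% |
| 7 cm, 0.25, 0% | 0.83 | 0.37 | 31% | 91% |
| 4 cm, 0.5, 10% | 0.64 | 0.44 | 61% | 57% |
| 3 cm, 0.5, 10% | 0.64 | 0.29 | 37% | 73% |

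The classes keep more than half in four of the seven. The three that lose more than half are those where 73% or more of participants share a class. Repeating both sets with new random numbers changed no power by more than about 2 points.

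**The case against.** Four points weigh against the concern.

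- **The centimetre value may be kept.** Section 3.5 says the diameter is measured and then classified; it does not say that the number is dropped or that only the class is analysed. Section 3.6 promises description of all measured variables. This stands, and it is why the point is conditional.
- **The choice of variable and test may sit in the analysis plan.** The article names no test, and a condensed article need not. That is fair for the test. It does not cover the outcome definition, which section 3.5 states, and states only as classes.
- **The scale is published and starts from presence.** Section 3.5 speaks of presence and occurrence, and the first class is none. If treatment mainly prevents bruises, the classes lose nothing. This stands. Whether the cut points have a clinical basis cannot be judged without the cited source.
- **The stakes are small.** Hematoma is one of several secondary outcomes, and the sample size does not depend on it. This also stands.

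A reader might infer that most of the difference between arms is lost. The documents do not support that. They give no diameter distribution, and under the assumed ones most of the information is kept unless participants are heavily concentrated in one class. Nor do they support predicting that a null result would be misread as no effect.

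**Conclusion.** The point holds in a limited, conditional form. If the class alone is kept and compared, information on bruise size is lost. The loss is about a fifth to a quarter of the efficiency when diameters spread well over the classes, a third or so in intermediate cases, and well over half when roughly three quarters or more of participants share a class. It is nil for an effect on presence alone.

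These figures rest on assumed log-normal diameters, assumed shares with no bruise, 33 per group and one value per participant. Nothing in the article shows which situation applies, and it may differ between day 1 and day 14.

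The primary outcomes and the sample size are unaffected. This is a cheap improvement to one secondary outcome, not a mistake in the plan.

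**What to change.** In section 3.5 and on the case report form, record the largest diameter in cm on each side at days 1, 2, 7 and 14, with 0 for none. Name the diameter as the variable on which the arms are compared, with a rank-based test. State how the two sides give one value per participant (for example, the larger of the two), so that sides are not counted as independent. Keep the four classes as a descriptive table by arm and visit, for comparison with the cited scale.

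**Cost:** one number per side per visit, from a measurement already made, and a line or two of text. There is no new procedure or visit.

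**Downside:** if the effect is purely on presence versus absence, there is no gain and possibly some loss of power (1 and 9 points in the two presence-only scenarios above). The descriptive table would still show such an effect.

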### Statistical analysis

3.6

Initial descriptive analyses will be performed considering all variables measured in the study, both quantitative (mean and standard deviation) and qualitative (frequencies and percentages). Later, the appropriate statistical tests will be applied for each specific analysis. In all tests, the significance level of 5% probability or the corresponding *P*-value will be adopted. All analyses will be performed using the statistical software SAS for Windows, version 9.1.

## Discussion

4

Two systematic reviews on the use of PBM after rapid maxillary disjunctions have recently been published.^[10,11]^ Both report that only 4 controlled and randomized clinical trials were conducted on the subject, and only one of them was performed with surgery.

Angeletti et al^[12]^ evaluated the effects of laser PBM on bone regeneration in the median region of the anterior suture after SARME. The authors observed that bone regeneration in the group receiving PBM was better in all experimental periods. Cepera et al^[31]^ evaluated the effects of laser PBM (GaAIAs, 780 nm, 40 mW, 10 J/cm^2^, 0.4 J per point) on bone regeneration and the success of orthodontic maxillary expansion using the Hyrax appliance. The authors concluded, after analysis of occlusal radiographs in 5 experimental periods, that the group that received PBM presented a greater expansion and better bone regeneration than the one that did not receive it. Garcia et al^[32]^ also studied the effects of PBM on repair of the medial palatine suture after maxillary orthodontic expansion. In the group that received PBM, the bone repair was superior. Finally, Ferreira et al,^[33]^ evaluated the effects of PBM on bone regeneration in the median palatine suture after rapid maxillary expansion using orthodontics (Hyrax type expander). Bone regeneration was assessed by measuring the OD in the images, and the authors also concluded that PBM positively influenced the bone regeneration of the medial palatine suture by accelerating the repair process.

Since PBM has shown positive effects on postoperative complications of other types of oral surgery^[7,8]^ and also has a positive effect on bone repair after maxillary disjunction, surgically assisted or not,^[10,11]^ it seems clear the need to evaluate its performance regarding pain, edema, and paresthesia after these surgeries. In addition, maxillary disjunction surgeries reach large anatomical areas involving intra and extraoral structures, so it also seems clear that there is a need to evaluate the performance of LED sources that can reach larger areas in the same application and combine wavelengths that are absorbed by superficial and deeper tissues.
